**7. SAFETY MEASURES**

Safety Measurement in Case of Adverse Events: Due to the double blind design of the study, the NIA/MRI Research Pharmacy will prepare and maintain the randomization schedule for the protocol. This randomization schema will be available at the NIA Clinical Research Unit Pharmacy. The Pharmacist will notify the PI of the specific participant’s randomization in case of any adverse events/emergency situations.

The definitions of adverse events (AEs) and serious adverse events (SAEs) are given below. All staff involved in this study will be familiar with the content of this section. The principal investigator is responsible for making sure that all personnel are adequately trained in the screening and recognition of these adverse events.

Adverse Event: An adverse event is the development of an undesirable medical condition or the deterioration of a pre-existing medical condition following or during exposure to a pharmaceutical product or medical intervention, whether or not considered causally related to the product. An undesirable medical condition can be symptoms (e.g., nausea, chest pain), signs (e.g., tachycardia, enlarged liver would this be noticed in this short period of time only PE is during visits 1 and 2, or the abnormal results of an investigation (e.g., laboratory findings, electrocardiogram). In the context of this study, the definition of an adverse event includes an undesirable medical condition occurring at any time, including run-in or washout periods, even if no study treatment has been administered.

Management of adverse event

In case of an emergent medical event the subject will be evaluated by the study NIA Clinical Research Unit medical team R.N., CRC, NP/PA, and MD. If needed the subject will be transferred to the Harbor Hospital emergency room and will receive appropriate evaluation and treatment.

Reporting of Adverse Events

All adverse clinical experiences, whether observed by the investigator or reported by the patient, must be recorded, with details about the duration and intensity of each episode, the action taken with respect to the test drug, and the patient’s outcome. The investigator must evaluate each adverse experience for its relationship to the test drug and for its seriousness. The investigator must appraise all abnormal laboratory results for their clinical significance. If any abnormal laboratory result is considered clinically significant, the investigator must provide details about the action taken with respect to the test drug and about the patient’s outcome.

Serious Adverse Event: A serious adverse event is an AE occurring during any study phase (e.g., run-in, treatment, washout, follow-up) and at any dose of the investigational product, comparator, placebo or medical intervention, that fulfills one or more of the following criteria:

- results in death
- is immediately life-threatening
- requires in-patient hospitalization or prolongation of existing hospitalization
- results in persistent or significant disability or incapacity
- results in a congenital abnormality or birth defect
- Any other important medical event that may jeopardize the subject or may require medical intervention to prevent one of the outcomes listed above.

The causality of SAEs (their relationship to study treatment) will be assessed by the investigator(s).

Reporting of Serious Adverse Events: Investigators and other site personnel will inform the FDA, via a MedWatch form, of any unexpected and possibly study drug related SAE that occurs according to the FDA reporting requirement timelines. A copy of the MedWatch report will be emailed to the MRI IRB through the NIA/IRP Protocol Office at the time the event is reported to the FDA. We are aware that it is the responsibility of the investigator to compile all necessary information and ensure that the FDA receives a report according to the FDA reporting requirement timelines and to ensure that these reports are also submitted to MRI IRB at the same time. A complete written SAE report will be sent with a cover page indicating the following:

- Rasburicase® or UA Investigator Sponsored Study (RISS)
- The investigator IND number assigned by the FDA
- The investigator’s name and address
- The trial name and the reference number

Sent to the NIA Clinical Research Protocol Office, Attention Rasburicase® or UA ISS Safety Representative. If a non-serious AE becomes serious, this and other relevant follow-up information must also be provided to the FDA.

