**3. Study Design and Methods**

This is a prospective placebo-controlled study, which consists of two inter-related trials, Trial A: UA versus Placebo and Trial B: Rasburicase versus Placebo respectively. Participants will be community-dwelling women and men, aged 50-75 years with BMI 23-34.9 kg/m2. All participants must be capable of attending an outpatient setting at the required protocol time-points.

Participants will be randomized into either Trial A or Trial B: Trial A: UA versus Placebo; and Trial B: Rasburicase versus Placebo. All specific inclusion/exclusion criteria are explained in detail in the remainder of this document.

According to the sequence of enrollment, eligible participants will be randomly assigned to treatment or placebo until 5 pairs of participants (1 intervention and 1 control subject) have been enrolled in each cohort (see the follow Enrollment schema). The randomization list will be maintained by the protocol study monitor. Two sealed copies of the randomization list will be stored at the NIA; one with the PI and one secured in the NIA Research Pharmacy. Study investigators and participants will be blinded to the treatment/placebo assignments. However, NIA research pharmacist or a person designated by him/her will not be blinded, since the medications will be prepared and dispensed to subjects from the NIA Research Pharmacy. The P.I. or designated NIA physician will review the laboratory results with the identity of the subject kept anonymous.

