**5. Procedures and Therapeutic Plan**

In each of the two Trials, 5 women and 5 men will be assigned to receive treatment and 5 women and 5 men will be assigned to receive placebo. There will be no recognizable labels treatment/placebo on the drug bag, and the NIA research pharmacist will be the only person unblinded to the random assignment to treatment or placebo.

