**Visit 3: Baseline and short-term post-intervention**

Visit 3 will be scheduled at least 2 days after Visit 2. Participants will be asked to arrive the evening before Visit 3 for a two consecutive overnight stay at the NIA Clinical ResearchUnit. Below is the sequence of exams and blood tests scheduled for Visit 3. As mentioned above, participants will be requested to drink at least two glasses of water and eat a light breakfast (cold cereal, milk, coffee or tea and bread and butter with butter and/or jelly in the morning). If for some reason, the study participant does not consume an appropriate amount of water on their own 500 mL of normal saline 0.09% will be administered intravenously prior to the study intervention. Based on their characteristics (UA serum level) and sequence of enrollment, participant will be assigned a randomization envelope. After opening the envelope and compiling the included randomization form, the NIA research pharmacist assigns the participant to the treatment or placebo group and prepares the study drug. Information on randomization will be maintained by the NIA research pharmacy in a safe but known place, accessible in case of emergencies. At 4:00 pm following the treatment, participants will eat a dinner consisting of a sandwich and a bag of chips. They may have a soda, coffee, tea or milk. The participant will be not be able to eat again until morning for the lipid tolerance test but will be given water freely.

*1. Basal Metabolic Rate (BMR)*

Basal Metabolic Rate will be estimated in Visit 3 at baseline and on the next day after the intervention. The measurement will be performed in the morning after overnight fasting at the NIA Clinical Research Unit. RMR will be measured before any other evaluation using the COSMED K4 b2 portable indirect calorimeter.

*2. Vital sign measurements*

Blood pressure, pulse rate, respirations and core body temperature will be measured at baseline and at each evaluation time during the following 24 hours. Pulse rate and blood pressure will be estimated using an automated cuff. Core temperature will be estimated using a sublingual thermometer. An EKG will be obtained 24 hours after the beginning of the infusion.

*3. Infusion of the Study Drug*

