Total and differential white and red blood counts, hemoglobin, hematocrit, platelets, glucose, BUN, creatinine, Uric Acid, LDH, CPK, electrolytes, AST, ALT, ALP, albumin, globulin, bilirubin (total and direct), haptoglobin, HDL and total cholesterol, triglycerides, and CRP will be drawn at the 24 hour timepoint to make sure that there has been no change post intervention. The total amount of blood needed for this will be 15 mL.

*11. Urine collection*

A urine sample will be collected at baseline (first morning void on Day 1), every void between 1 and 12 hours after infusion and 24 hours after infusion. The urine samples will be used to evaluate uric acid levels in the urine and potentially markers of oxidative stress damage.

*12. MRI muscle spectroscopy.*

Magnetic resonance spectroscopy (MRS) will be used to study energy metabolism in muscle during and after exercise. As already mentioned, MRS is performed once on Visit 2 and a second time 24 hours after the infusion of the study drug, immediately before performing the second Lipid Tolerance Test. Participants will be carefully screened for MRI contraindications before performing the tests. Also, they will be given a choice of receiving the MRI. Participants with contraindication to MRI or refusing MRI will not receive MRI but will be still enrolled in the other parts of the study, without any effects on their compensation.

*13. Lipid Tolerance Test*

24 hours after the injection, A second OLTT will be performed using exactly the same protocol used in Visit 2.

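### Section 7 discloses a participant's arm to the PI for any adverse event, which contradicts the double blind and the emergency code access stated elsewhere in the protocol

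*Protocol*

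**What the plan says.** **Disclosure rule.** Section 7 (Safety Measures) has the pharmacist tell the PI a participant's "randomization in case of any adverse events/emergency situations". The definition that follows covers symptoms (nausea is one of its examples), signs and abnormal investigations, related to the product or not, and "includes an undesirable medical condition occurring at any time, including run-in or washout periods, even if no study treatment has been administered".

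**Blinding.** Section 3 states that investigators and participants are blinded. Section 5 describes administration as double-blind and says that "the NIA research pharmacist will be the only person unblinded to the random assignment to treatment or placebo".

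**Emergency access.** Section 5, Visit 3: "Information on randomization will be maintained by the NIA research pharmacy in a safe but known place, accessible in case of emergencies".

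**Custody of the list.** Section 3 gives maintenance of the list to the study monitor, with two sealed copies, "one with the PI and one secured in the NIA Research Pharmacy". Section 7 says the pharmacy prepares and maintains the schedule.

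**Allocation.** Section 3 assigns by order of enrolment "until 5 pairs of participants (1 intervention and 1 control subject) have been enrolled in each cohort". No block size is stated.

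**Laboratory results.** Section 3 has the PI or a designated physician review results without the subject's identity. The Visit 3 follow-up panel, which includes uric acid, "will be drawn at the 24 hour timepoint to make sure that there has been no change post intervention".

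**The concern.** Section 7 sets the threshold for opening the code at an ordinary adverse event. With a definition this wide, a mild complaint or an out-of-range laboratory value after randomisation would be enough for the PI to be told the arm. That is incompatible with a trial in which only the pharmacist is unblinded.

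Several judgements would then be open to knowledge of the arm:
- Investigators assess the relationship of each adverse event to study drug (Section 7).
- The PI decides on clinical judgement whether the study should stop (Section 8).
- The PI may exclude a candidate at discretion (Section 4b, item 29).
- Inflammatory markers may be dropped or substituted at study end (Section 5, Visits 2 and 3). The protocol does not say who makes that choice.

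**Working it through.** **1. The rules side by side**

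| Place | Who may know the arm, and when |
|---|---|
| Section 3 | Investigators blinded; pharmacist or designee not blinded |
| Section 5, opening paragraph | Pharmacist only |
| Section 5, Trial B paragraph | Double-blind; pharmacist or designee only |
| Section 5, Visit 3 | Code held by the pharmacy, accessible in emergencies |
| Section 7 | PI told for any adverse event or emergency |

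The first four rows are compatible apart from the small matter of the designee. The fifth conflicts with them whenever an adverse event is not an emergency.

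**2. When the rule can act.** The schedule places randomisation at Visit 3 baseline. An event at Visit 1 or 2 therefore has no arm to reveal, despite the wide definition. Triggers after randomisation are plausible: Section 6 lists lightheadedness and bruising from blood draws, and rare nausea, vomiting or diarrhoea from the fatty meal. Both procedures take place after the infusion in every arm.

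**3. How often.** The plan's total is reproduced first: 2 trials × 2 sexes × 5 pairs × 2 = 40, as in Section 11. This holds only if the cohort in Section 3 means a sex group within a trial; read as a whole trial, it gives 2 × 5 × 2 = 20.

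The protocol gives no adverse event rate for this population. Let p be an assumed probability that a participant has at least one event after randomisation, independent between participants. Expected disclosures are 40p, and the chance of at least one is 1 − (1 − p)^40. If pairs were blocks of two, each disclosure would also reveal the partner, so the expected number of known arms would be 40 × [1 − (1 − p)²].

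| Assumed p | Expected disclosures | Chance of at least one | Arms known if blocks of two |
|---|---|---|---|
| 2% | 0.8 | 55% | 1.6 |
| 5% | 2 | 87% | 3.9 |
| 10% | 4 | 98.5% | 7.6 |

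**4. Predictability of the next assignment.** If every earlier arm in a cell of 10 were known, the best guess would be right in (0.5 + 1)/2 = 75% of cases with blocks of two. With one 5:5 block it would be right in 5 + (2^10/252 − 1)/2 = 6.53 of 10, or 65%. If the arms stay masked, it is 50% under either scheme. Predictability therefore follows from disclosure and does not arise alone.

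**5. Uric acid at 24 hours.** In Trial B, Section 11 postulates that uric acid goes to zero on rasburicase, so a near-zero value would point to the active arm. In Trial A, the rise is 2.5–3 mg/dL (Section 11) to 3–4 mg/dL (Section 6), and the half-life is 10.8 h (Section 14).
- Exponential decay: the factor is 0.5^(24/10.8) = 0.214, which leaves 0.54 mg/dL of 2.5 and 0.86 of 4.
- Linear return from 2 h to 48 h: the factor is 24/46 = 0.52, which leaves 1.3 to 2.1 mg/dL.

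No standard deviation for uric acid change is given, so the protocol does not show whether this would reveal a Trial A arm.

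**The case against.** **The slash may mean emergencies.** The phrase could be meant for adverse events that are emergencies, which would agree with the Visit 3 text. But Section 7 names any adverse event first and defines the term broadly straight afterwards. At best the sentence is ambiguous on who is unblinded and when.

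**The impact is limited.** This stands in large part. The markers are assayed from banked samples sent out at study end (Section 5), treatment is a single infusion, and causality is not an endpoint of this physiological pilot. Eligibility is reviewed at Visits 1 and 2, and the pharmacist opens the envelope at Visit 3. Discretionary exclusion could therefore affect group composition only if earlier disclosures made a later arm guessable.

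**Stronger readings.** A reader might infer that the blind fails by several further routes. The text does not support that.
- *The PI holds the list.* The PI's copy is sealed. This is a weakness of custody and discloses no arm.
- *The PI sees uric acid by participant.* Section 3 provides for review without identity, and nothing says that participants are admitted one at a time. A risk remains in Trial B, because Section 7 requires action and outcome to be recorded for clinically significant abnormal results and the Visit 4 text ties a 4-week visit to an individual's uric acid.
- *The next assignment is predictable.* The pairs may be only a stopping count, and the 75% figure needs every earlier arm to be known.

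**Conclusion.** The contradiction is real and rests on the current wording alone: Section 7 cannot be followed together with Sections 3 and 5. Followed literally, it would probably unblind the PI for at least one participant even at low event rates (55% at 2%, 87% at 5%). These rates are assumptions, and the chances also assume independent events and literal application.

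What is exposed is blinded judgement of causality, the decision on stopping the study, discretionary exclusion and possibly the choice of markers at study end. Measurement of the primary outcome is little exposed.

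The 24-hour uric acid in Trial B and the possible blocks of two are secondary risks. It would be wrong to conclude that either one, or the sealed list copy, breaks the blind in itself. The point should be corrected, but it does not undermine the design.

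**What to change.** Reconcile Section 7 with Sections 3 and 5, so that the code is opened only under the emergency access the Visit 3 text already provides and non-emergency adverse events are assessed blind. What counts as an emergency is for the clinical team to define.

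In the same amendment:
- State one custodian for the randomisation list, since Section 3 names the study monitor and Section 7 the pharmacy. The PI's sealed copy is better held by the pharmacy.
- Reconcile the anonymised laboratory review in Section 3 with the participant-level action required by Section 7 and the Visit 4 text, with Trial B uric acid in mind.
- Clarify, in a document kept from investigators, whether the pairs are blocks of two.

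A different block size gains little once disclosure is restricted, because masked arms give 50% under either scheme. Routing uric acid to pharmacy staff is not recommended: it would conflict with the investigator's duty in Section 7 to appraise all abnormal results, and would shift clinical follow-up.

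The cost is protocol wording. No participants, samples or visits are added.

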**8. GRADING AND MANAGEMENT OF TOXICITY**

Management of Unwanted/Emergent Medical Events: In case of an emergent medical event the subject will be evaluated by the study/NIA Clinical Research Unit medical team R.N., CRC, NP/PA, and MD. If needed the subject will be transferred to the Harbor Hospital emergency room and will receive appropriate evaluation and treatment.

Reporting Serious and Unexpected Side Effects: Serious and unexpected side effects will be immediately reported to the principal investigator. He will inform the NIA Protocol Office and they will notify the MedStar IRB in the time frame mandated by their guidelines.

Serious and Unexpected Side Effects Data Collection and Evaluation: Data of serious and unexpected side effects will be collected separately. The principal investigator will monitor the data any time clinical/laboratory data is added, and at the end of a certain dose phase, will decide according to his clinical judgment whether there is need for stop the study.

**9. STUDY END POINTS AND MONITORING**

Primary end point

The primary outcome is to ascertain whether UA is a pro-inflammatory compound. This aim will be tested both by measuring the concentration of inflammatory markers after short term changes in UA, and by testing the hypothesis that different concentrations of UA modify the inflammatory response induced by a lipid tolerance test.

Secondary Objectives

To document the effect of increasing versus decreasing UA levels on circulating antioxidant biomarkers. To test the hypothesis that increasing levels of UA are associated with higher mitochondrial efficiency as indicated by higher MRI-spectroscopy estimated rate of phosphocreatinine resynthesis after exercise.

An accrual ceiling of 200 men and women aged 50-75 years is expected in order to assure we have 40 subjects completing the study. The subjects participating in the study will be monitored closely during the study as noted above and will be followed-up until UA plasma levels return to baseline.

**10. Criteria for Withdrawal of Subjects from the Study**

Participation in both study trials may be stopped by the P.I. or the National Institute on Aging without subject consent at any time if:

1. The P.I. believes that stopping participation is necessary for the subject’s health and safety

2. The subject fails to follow the study instructions

3. The National Institute on Aging decides to terminate the study

4. Administrative reasons require the subject to withdraw

5. The subject decides to withdraw from the study. Any data or blood collected until that point in time would remain part of the study.

A subject may stop participating at any time. However, we would encourage them to first talk to the researcher and their own doctor before the final decision.

**11. Statistical Considerations**

Sample size procedure specifications: as this is a pilot trial aimed at understanding the physiological parameters rather than clinical safety or efficacy endpoints, we estimated the sample size (number of subjects per arm; total number of subjects) as follows:

A. We determined the inter-assay coefficient of variation (CV) of the main laboratory assays of IL-6 which is the reference inflammatory marker identified in this study;

B. We considered that any value demonstrating a difference greater than 3 x CV in each laboratory parameter/endpoint between baseline and post-intervention (in both Trials A and B) would be of biological significance. The obtained CV was indirectly included in the sample size definition by affecting the variability of expected changes in UA we estimated to observe after treatment.

C. We estimated the sample size by Monte Carlo (41) study applied to a mixed effect model (42) using R software (43). The form of the mixed effects model was

**y(ij)=a+a0(i) + b1*factor(time(j))+b2*treatment(i)+ e(ij).**  In this model, ‘i’ refers to subject, j to time, and a0(i) to the random intercept for subject i. We aimed at estimating a big enough sample per arm to have a high likelihood of detecting a true difference between two groups.

These sample size procedure specification is based on previous findings from Waring and our group. Waring et al. showed that infusions of 1,000 mg and 500 mg of UA were associated with an increase of UA circulating levels of 3.2-4.9 mg/dL with this increase persisting for 10-12 hours. For the purpose of the power analysis, we assumed a very conservative increase in UA of 2.5-3 mg/dL persisting from 2 to 12 hours, and a progressive decline in UA levels after 2 hours returning to baseline by 48 hours. The control group was assumed to show no systematic change in UA (16,18, 19). Further, the report by Ruggiero et al found that IL6 increased by 0.08 per mg/dL increase of uric acid. We examined an associated increase of 0.04, 0.06 and 0.08 pg/ml for each mg/dL change in UA. Using these relationships, IL-6 was sampled at each point in time from a normal distribution with a standard deviation as found in Ruggiero et al. of 0.02 for a sample size of 976 subjects (21). The resulting IL-6 was entered into a mixed effects model being regressed on time and group with subject as a random effect. This model was compared to a model including group using a log-likelihood test, and the null was accepted at p> 0.05. The simulation was repeated 100 times to determine the number of times the null hypothesis was rejected. For 10 subjects per group, with a rise in UA of 2.7 mg/dL, a coefficient of 0.04 gave a power of 0.94, a coefficient of 0.06 gave a power of 0.98, and a coefficient of 0.08 gave a power of 1.00. For rasburicase, we postulated that UA would go to zero. With the current model, UA increase of 2.0 with progressive decrease over time gives power of 0.92, 0.93, 0.93 for the coefficients of 0.04, 0.06 and 0.08. UA increase of 1.5 had a power in the 0.6-0.7 range for the 3 coefficients.

With this assumption, 10 subjects per group resulted in a power of 0.97 for a coefficient of 0.04, 1.00 for a coefficient of 0.06, and 1.00 for a coefficient of 0.08.

Enrollment: a total of 40 participants will be enrolled. According to inclusion/exclusion criteria 20 participants, 10 men and 10 women, will be recruited in Trial A: Uric Acid versus placebo trial and 20 participants, 10 men and 10 women, in Trial B: Rasburicase versus placebo trial. To maintain the number of participants as above, we will screen 6 more subjects, (3 men and 3 women for each cohort), that will be enrolled only if some drop-outs occur.

Randomization to treatment or placebo: according to the order of enrollment and sex, participants will be randomly assigned to receive treatment or placebo in each cohort.

Data analysis: differences in circulating inflammatory markers and antioxidants, as well as differences in other measurements will be estimated before and after treatment in both cases and controls. In each trial, the time-dependent modification of UA levels will be evaluated and the outcomes will be estimated and compared between cases and controls after intervention.

